### Recruitment/Randomization

2.3

Project staff will contact local community agencies serving adults with DS, case managers, and Community Developmental Disabilities Organizations by mail/email, provide presentations at community agencies and local events, and distribute newsletters describing the project. Interested parents/guardians, caregivers, or adults with DS will be asked to contact the study coordinator via email, our website, or a dedicated toll‐free study phone number that will be included in all recruitment materials. The study coordinator will contact the interested individuals by phone to answer questions and conduct an initial eligibility screen. Video conference visits will be scheduled with those remaining interested, and potentially eligible, to obtain informed consent (participants or legal guardian) and participant assent (if not their own legal guardian) and determine final eligibility based on the DSQIID scores. Participants found to be ineligible will be provided with written materials describing available resources for weight loss. Participants will be stratified by age (18–30 vs. > 30 years) and sequentially computer‐randomized by the study statistician with 2:1 allocation to the weight loss or control arms. This randomization scheme was selected to include more participants in the weight loss arm which will allow for a larger sample size to assess the association of weight loss and changes in dietary intake with changes in biomarkers and cognitive function. Intervention assignments will be concealed and delivered to the study coordinator prior to participant orientation sessions described below.

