#### Sample size

2.9.1

The primary aim is to estimate the effect of a 12‐month weight loss intervention relative to control to determine if the intervention impacts relevant outcome variables, and if so, to precisely quantify the observed effect. The sample size was estimated using simulation with regard to plasma NfL based on the observation that changes in this biomarker is an early marker of AD in adults with DS.^2^ A recent 2021 paper reported an annual change in NfL of 3% in asymptomatic non‐progressive AD patients.^43^ Thus, we simulated annual data at baseline, 6 and 12 months assuming an average 3% annual increase in NfL for all participants in the control arm and an average change of 1.35% in the intervention arm which corresponds to a “small” Cohen's h effect size of 0.12. We modeled the between arm difference in NfL using a linear mixed model with a random intercept for each participant; with a sample size of 81 (*n* = 54 intervention; *n* = 27 control) and an estimated attrition rate of 20%. With these assumptions, we will be able to estimate the precision of the difference in the annualized increase in NfL with a 95% confidence interval of width 3%. Similar mixed models will be fit for all seven outcome variable categories to estimate the effects across all the domains of interest. A major concern with using estimated effects from pilot studies to power larger trials is that they are highly variable. This sample size and approach will guarantee good precision for our estimates which is especially important considering that there are currently no data regarding clinically relevant changes to use for powering a larger trial.

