#### Analysis

2.9.2

We will assess plasma biomarkers related to AD, cardiometabolic biomarkers, cognitive function, energy and macronutrient intake, and diet quality at baseline, 6 and 12 months. We will assess cerebral antioxidants and brain volume at baseline and 12 months. We will calculate the mean, standard deviation, and 95% confidence intervals in both the intervention and control arms for each of these outcome variables at each time point, and for the change from baseline to each time point. This descriptive information will be summarized graphically which will aid in determining if, and when, differences in outcome variables arise among and across the two arms. Linear mixed models with an autoregressive correlation structure and a random intercept for each participant will be used to model the longitudinal serial correlation and baseline between‐subject variation. The model will include a main effect for intervention arm, and time and an arm‐by‐time interaction. The point estimate and 95% confidence interval for the arm‐by‐time interaction evaluated at both 6 and 12 months will be used to estimate the between arm effect size. Mixed models will be adjusted for age, sex, ethnicity/race, MVPA, premorbid ID, number of study participants living in the same household, intervention attendance, and intervention arm. Model fit will be assessed using diagnostic plots and comparing likelihood values between alternative model formulations or transformations, when appropriate. No multiplicity adjustment will be conducted since no hypotheses will be tested.

To determine the independent effects of weight loss or diet quality on changes in plasma biomarkers related to AD (Aβ 42/40, pTau217, and NfL), cerebral antioxidants, brain volume, cardiometabolic biomarkers, and cognitive function we will conduct a set of nested likelihood ratio tests (LRT). The goal of this analysis is to determine if weight loss, diet quality or both should be targeted in future trials for the prevention of AD in adults with DS. No adjustment for multiple testing will be conducted because rejection of any of the nested comparisons will imply that a change in a greater number of underlying covariates, for example, weight loss and diet compared to weight loss alone are needed to elicit changes in biomarkers.

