Completion of this project represents an initial step toward developing and disseminating effective interventions to prevent or delay the development of AD in adults with DS. This trial will provide preliminary data on the impact of weight loss and improved diet quality on cognitive function and factors associated with the development of AD and the time course of any changes in adults with DS. Additionally, results of this study could help inform dietary guidelines for adults with DS. If the results of this pilot are positive, that is, improvements in some or all AD associated outcomes assessed we will propose an adequately powered randomized trial to further investigate the impact of weight loss and diet quality on these outcomes in adults with DS. If our pilot results suggest an independent effect of diet quality on factors associated with AD we will also propose an adequately powered randomized trial to investigate the impact of improved diet quality without weight loss on AD outcomes. Subsequent trials may include additional AD markers obtained from cerebrospinal fluid (CSF) or PET scans.

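### Aim 3 can answer weight loss alone or diet quality alone only through a non-significant test of the other factor, and the sample was not sized for that reading

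*Protocol article*

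**What the plan says.** Table 1 of the protocol article describes Aim 3 as exploring the independent effects of weight loss or diet quality. Section 2.9.2 (Analysis) gives that work a decision to make: "The goal of this analysis is to determine if weight loss, diet quality or both should be targeted in future trials". The method is a set of nested likelihood ratio tests (LRTs). The only interpretation offered is for a significant result: "rejection of any of the nested comparisons will imply that a change in a greater number of underlying covariates" is needed, with weight loss plus diet against weight loss alone as the example. Nothing is said about what a non-significant comparison means.

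Section 2.9.1 (Sample size) derives the numbers from a simulation of NfL change between arms, "with a sample size of 81" and 20% attrition. It also says that no data exist on clinically relevant changes. Section 3 (Discussion) attaches a consequence to Aim 3: "If our pilot results suggest an independent effect of diet quality on factors associated with AD we will also propose" a separate trial of diet quality without weight loss.

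**The concern.** Of the three answers that the analysis is meant to choose between, only *both* can follow from rejection of the second-factor tests. *Weight loss alone* requires that adding diet quality to a model with weight change is not significant. *Diet quality alone* requires the reverse. In each case the omitted factor is set aside because a test failed to reject, and no interval or estimate for it enters the stated reasoning.

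That is weak ground in a trial of this size. One intervention produces both weight change and diet change, so the two are likely to be correlated, and the separate effect of each is then estimated less precisely than either would be on its own. If a real independent effect is missed, the statement on what to target would be wrong, and the extra diet-quality trial might not be proposed.

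**Working it through.** **The plan's own figures.** The stated Cohen's h reproduces: 2·asin(√0.03) − 2·asin(√0.0135) = 0.348 − 0.233 = 0.115, which rounds to 0.12. The stated confidence interval width of 3% cannot be reproduced, because no SD or within-person correlation is given. Both figures concern the between-arm NfL contrast. No figure is given for the nested tests.

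**Inputs from the article.** 81 randomised and 20% attrition give 81 × 0.8 = 64.8, about 65 completers. Plasma, cardiometabolic, cognitive and diet measures are taken at baseline, 6 and 12 months. Imaging is at baseline and 12 months only, at an optional visit (section 2.7, Table 3).

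**Assumptions (not in the article).**
- Each factor enters as one continuous term, tested at the 5% level.
- The partial effect of diet is b = 0.3 SD of outcome change per SD of diet change, and weight has no effect of its own. This corresponds to about 2 × 0.798 × 0.3 = 0.48 SD between participants above and below the median diet change.
- The diet-weight correlation ρ is 0.3, 0.5 or 0.7.
- Residual variance is 1 − 0.3² = 0.91.

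**Miss rate, one change score per person.** Noncentrality λ = n·b²·(1 − ρ²)/0.91, and miss rate ≈ Φ(1.96 − √λ).

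| ρ | λ (n = 65) | √λ | Miss, formula | Miss, simulated LRT |
|---|---|---|---|---|
| 0.3 | 65 × 0.09 × 0.91/0.91 = 5.85 | 2.42 | 32% | 34–35% |
| 0.5 | 65 × 0.09 × 0.75/0.91 = 4.82 | 2.20 | 41% | 41–43% |
| 0.7 | 65 × 0.09 × 0.51/0.91 = 3.28 | 1.81 | 56% | 54–58% |

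Across both methods the range is 32% to 58%.

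**Both factors truly active at 0.3 SD.** By simulation at ρ = 0.3, 0.5 and 0.7, the pair of tests keeps exactly one factor in about 45%, 55% and 70% of trials. It finds both in about 50%, 40% and 18%.

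**Both follow-up visits used.** With residual correlation re between the two change scores and covariate correlation rx, information rises by k = (2 − 2·re·rx)/(1 − re²). For re 0.3 to 0.7 and rx 0.5 to 0.9 (assumed), k runs from 1.45 to 2.55. Multiplying λ by k gives miss rates of about 3–17%, 6–25% and 18–41% at ρ = 0.3, 0.5 and 0.7. For example, at ρ = 0.5, 4.82 × 1.45 = 6.99, √6.99 = 2.64, and the miss rate is 25%.

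**Imaging subsample.** The size is not stated. At an assumed n = 32, λ = 2.88, 2.37 and 1.61, and the miss rates are about 60%, 66% and 75%.

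**Sensitivity to the effect.** In terms of partial correlation at n = 65 with one change score, the miss rate runs from 87% at 0.10 through 63% at 0.20 and 30% at 0.30 to 7% at 0.40.

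**Interval width.** Half-width = 1.96·√(0.91/(65·(1 − ρ²))) = 0.23, 0.24, 0.27 and 0.32 SD at ρ = 0, 0.3, 0.5 and 0.7. A null estimate at ρ = 0.5 would exclude 0.3 SD but not 0.25 SD. At ρ = 0.7 it would not exclude 0.3 SD.

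**The case against.** The strongest reply is that the article never treats non-rejection as proof. A reader might infer that it does, or that a factor will be dropped from future work on a non-significant test, but the text says neither. Aim 3 is labelled exploratory, the trial is called a pilot, and a condensed article may leave the reading of non-significant tests to an analysis plan. All of that stands. What remains is that the article itself states a three-way choice as the goal and gives a meaning to one test result only.

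A second reply concerns the harm. A reader might infer that a missed factor would disappear from the next trial. Section 3 does not support this: if the pilot is positive, the main follow-on trial is to study weight loss and diet quality together, with no condition on the nested tests. The diet-only trial is additional, and its trigger is a result that suggests an independent effect, which is looser than rejection at 5%. This reply stands and narrows what is exposed.

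Third, the miss rates depend on an assumed effect, test level and correlation, and on one change score per person. Using both visits lowers them considerably for most outcomes. This also stands, so the figures illustrate and do not describe a property of the plan.

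A reader might also see a contradiction with the remark in section 2.9.2 that no hypotheses will be tested. That remark closes the paragraph on the between-arm models. The Aim 3 paragraph openly plans tests, so the remark lends no support here.

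**Conclusion.** The point holds in a limited form. As written, an answer of weight loss alone or diet quality alone rests on a non-significant test of the other factor, and the sample size was not set for these partial effects. This follows from the text and needs no assumed effect.

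The size is illustrative. With 65 completers, one change score, a 5% level, a 0.3 SD partial effect and correlation 0.3 to 0.7, diet given weight is missed in about 32% to 58% of trials. With both follow-up visits the figure falls to about 3% to 41% under the assumed correlations. For 12-month imaging with an assumed 32 participants it rises to about 60% to 75%. An unconditional miss rate cannot be stated, because the article defines no relevant effect.

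Exposed are the targeting conclusion in section 2.9.2 and the additional diet-quality trial in section 3. The main follow-on trial is not.

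**What to change.** In section 2.9.2, base the Aim 3 conclusion on the joint model's partial coefficients for weight change and diet-quality change, each with a 95% confidence interval, using all follow-up visits where the outcome has them. Keep the nested LRTs as supportive. Add a sentence such as: *A non-significant likelihood ratio test alone will be reported as not separable with this sample and will not be grounds for dropping a factor from future trials.*

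An equivalence margin of ±0.2 SD would not be a workable addition. The expected half-width on a single change score is 0.23 SD even with uncorrelated factors and 0.27 SD at correlation 0.5, so the interval could practically never fall inside it.

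The cost is a change of wording and a table of coefficients from models close to those already planned. The downside is that many outcomes will be reported as inconclusive on which factor matters.

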#### Visit 2: Neuroimaging (optional)

2.7.2

This visit will last approximately 1 h and occur at baseline and 12 months. Scanning will be performed on a 3T Siemens Skyra scanner using a 20‐channel head coil. A T1‐weighted structural scan will be completed using 3D multi echo MPRAGE (MEMPRAGE) with real‐time motion correction and selective reacquisition^36^ (repetition time/inversion time/echo time [TR/TI/TE] = 2500/1300/1.79,3.65,5,51,7.37 ms, flip angle = 7°, field of view [FOV] = 256, matrix = 256 × 256 × 176, resolution = 1 mm^3^, scan time = 6.5 min). Volumetric analysis will be performed using segmentation and brain region parcellation pipelines implemented in FreeSurfer.^37^, ^38^ Regions of interest will include white matter, total gray matter, total intercranial volume, and hippocampal volume. To explore how the diet intervention impacts nutrient concentrations in the brain, brain glutathione (GSH)^39^ and vitamin C^40^ scans will be performed in an axial slice covering frontal and parietal regions using the doubly‐selective multiple quantum (MQ) CSI sequences with real‐time motion/shim correction (TE/TR = 115/1750 ms for GSH, TE/TR = 124/1750 ms for vitamin C, FOV = 20 cm, matrix = 10 × 10, slice thickness = 2.5 cm, scan time = 11.5 min each). Previous research in cognitively normal older adults suggest dietary interventions can lead to significant changes in GSH levels in as little as 12 weeks.^41^ Brain antioxidant signals will be quantified using the internal concentration reference method utilizing unsuppressed brain water signals. We will use previously established quantification procedures using in‐house data processing program written in Interactive Data Language (IDL; L3Harris, Bloomfield, CO, USA).^39^ Brain GSH and vitamin C concentrations in each voxel will be corrected for partial volume effect due to brain atrophy using effective tissue volume fraction calculated from magnetization‐prepared rapid gradient echo (MPRAGE) magnetic resonance imaging (MRI).^42^ We will use all the voxels that pass the preset criteria for spectral quality and tissue volume fraction in both region‐of‐interest analysis^39^ and voxel‐based analysis. We will also determine antioxidant concentrations in gray and white matter using well‐established regression‐based methods^42^ to examine potential differences of antioxidant concentrations in gray and white matter, and differential changes in gray matter and white matter after intervention.

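### The reason given for leaving the Aim 3 nested likelihood ratio tests unadjusted is invalid, and a rejection is read as showing more than it can

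*Protocol article*

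**What the plan says.** Section 2.9.2 (Analysis) has two paragraphs, each with its own statement on multiplicity.

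- The first covers the mixed models, which yield arm-by-time estimates and 95% confidence intervals. It ends: "No multiplicity adjustment will be conducted since no hypotheses will be tested".
- The second covers Aim 3, the separate contributions of weight loss and diet quality. For this, "we will conduct a set of nested likelihood ratio tests (LRT", over Aβ 42/40, "pTau217, and NfL), cerebral antioxidants, brain volume, cardiometabolic biomarkers, and cognitive function". The purpose is stated: "The goal of this analysis is to determine if weight loss, diet quality or both should be targeted in future trials". Adjustment is waived on a different ground: "No adjustment for multiple testing will be conducted because rejection of any of the nested comparisons will imply" that changes in more of the covariates, for example weight and diet rather than weight alone, are required to alter the biomarkers.

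The Discussion (Section 3) says what may follow. The pilot counts as positive on "improvements in some or all AD associated outcomes assessed we will propose an adequately powered randomized trial". On diet it says: "If our pilot results suggest an independent effect of diet quality on factors associated with AD we will also propose" a trial of better diet quality without weight loss.

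**The concern.** The Aim 3 waiver rests on what a rejection would mean, not on how often a false one would occur. Two things are wrong with it.

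**Error rate.** That one model is nested in another says nothing about the number of outcomes on which the comparison is repeated. If a rejection of any comparison is taken as informative, the chance that at least one is false grows with the number of tests. A fixed testing order could protect the error rate within one outcome. The article states no such order, and it would not protect across outcomes.

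**Interpretation.** Weight change and diet quality during follow-up are not randomised; only the arm is. Rejecting the weight-only model in favour of weight plus diet shows that diet is associated with the outcome given weight. It does not show that both changes are required to produce an effect.

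The stake is the stated purpose of Aim 3, which is to settle whether weight, diet or both are pursued next. A false lead in one of many outcomes could steer that choice.

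**Working it through.** **The plan's own figure.** There is none to reproduce. The article gives no number of tests, significance level or family-wise error rate for the likelihood ratio tests.

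**Inputs counted from the article**

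| Domain tested under Aim 3 | Outcomes | Where |
|---|---|---|
| Plasma AD markers | 3 (Aβ 42/40, pTau217, NfL) | Section 2.9.2 |
| Cerebral antioxidants | 2 (glutathione, vitamin C) | Section 2.7.2: "Brain GSH and vitamin C concentrations in each voxel will be corrected for partial volume effect" |
| Brain volume | 4 regions | Section 2.7.2 |
| Cardiometabolic | 4 (lipids, glucose, HbA1c, inflammatory markers, each counted once) | Section 2.7.1, Blood draw |
| Cognition | 3 directly administered tests; 7 with the four informant scales | Sections 2.1 and 2.7.1 |

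Total: 3 + 2 + 4 + 4 + 3 = 16, or 16 + 4 = 20 with the informant scales.

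**Assumptions.** Level 0.05 per test; all null hypotheses true; two comparisons per outcome (diet added to weight, weight added to diet), with one per outcome and domain-level testing as smaller cases.

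**Independent tests.** Chance of at least one false rejection = 1 − 0.95^m; expected number = 0.05m.

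| Case | m | Chance of at least one | Expected number |
|---|---|---|---|
| 5 domains × 2 | 10 | 0.40 | 0.5 |
| 16 outcomes × 1 | 16 | 0.56 | 0.8 |
| 20 outcomes × 1 | 20 | 0.64 | 1.0 |
| 16 outcomes × 2 | 32 | 0.81 | 1.6 |
| 20 outcomes × 2 | 40 | 0.87 | 2.0 |

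**Correlated outcomes.** Outcomes measured in the same people are correlated, so independence gives the upper end. A simulation of 100,000 replicates used normal test statistics with exchangeable correlation between outcomes. The correlation between the two tests on one outcome was set to 0 or −0.5; the ranges cover both settings.

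| Between-outcome correlation | 1 test each (16; 20 outcomes) | 2 tests each, 16 outcomes | 2 tests each, 20 outcomes |
|---|---|---|---|
| 0 | 0.56; 0.64 | 0.78–0.81 | 0.85–0.87 |
| 0.3 | 0.48; 0.54 | 0.70–0.73 | 0.77–0.79 |
| 0.5 | 0.37; 0.42 | 0.58–0.61 | 0.63–0.66 |
| 0.7 | 0.26; 0.29 | 0.43–0.46 | 0.47–0.50 |

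The lowest value, 0.26, is about five times the nominal 0.05.

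**The case against.** The strongest defence is the status of the study. Table 1 words Aim 3 as exploration, the Discussion calls the trial exploratory and a pilot, and the result of a false lead would be a proposal for an adequately powered trial that would itself test it. Unadjusted testing is acceptable in that setting when it is labelled as such, and this part of the defence stands. It does not rescue the waiver, because Section 2.9.2 does not appeal to exploratory status. It gives a specific inferential reason, and that reason is wrong. It is also fair that the level, the model order and the number of tests may be fixed in an analysis plan that is not shown, which is why the size is given as a range.

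Four stronger readings are tempting, and the article does not support them.

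- *The two paragraphs flatly contradict each other.* The sentence that no hypotheses are tested closes the mixed-model paragraph and can be read as limited to it; the Aim 3 tests have their own waiver. The sentence needs an explicit scope, no more.
- *Any single rejection triggers a new trial.* The article does not say so. A rejection is said to bear on which changes matter, and a diet trial would follow if results suggest an independent effect.
- *The statement about improvement in some outcomes can hardly fail.* That holds only if any favourable movement counts as improvement, and the article does not define the term. If improvement meant a 95% interval excluding zero in the favourable direction, also an assumption, the null chance for four independent plasma markers would be 1 − 0.975^4 = 0.10.
- *The trial must adopt one decision outcome, NfL, under Holm.* NfL is used in Section 2.9.1 for sizing, not as a criterion for going on. The stated interval width of 3% implies a standard error of 3/(2 × 1.96) = 0.765 points. The assumed difference is 3 − 1.35 = 1.65 points, so the chance that the interval excludes zero is Φ(1.65/0.765 − 1.96) = 0.58. Such a rule is an option, not a correction that the text requires.

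**Conclusion.** The concern holds for the Aim 3 likelihood ratio tests. The stated ground for not adjusting is invalid, and the stated meaning of a rejection goes beyond what a comparison of non-randomised changes can show. With 16 to 20 outcomes and two tests each at an assumed 5% level, the chance of at least one false rejection is about 0.81 to 0.87 under independence and 0.43 to 0.50 at correlation 0.7. Ten independent domain-level tests give 0.40, and one test per outcome at correlation 0.7 gives 0.26 to 0.29. The counts, the level and the correlations are assumptions, but inflation is material throughout the range.

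The fault lies in a stated inference rule meant to guide what future trials target. It is not a fault in running unadjusted exploratory analyses in a pilot.

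**What to change.** In Section 2.9.2:

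1. Delete the rationale that a rejection of any nested comparison justifies no adjustment.
2. Label the likelihood ratio tests as exploratory hypothesis tests not controlled for multiplicity, or control the false discovery rate across outcomes.
3. Report the partial coefficients for weight change and diet quality, with 95% confidence intervals, for every outcome.
4. Replace the claim of necessity with the statement that one change is associated with the outcome given the other.
5. Limit the sentence about no hypotheses being tested explicitly to the mixed-model estimates, since Aim 3 does test hypotheses.

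In Section 2.9.2 and the Discussion, base the choice of future target, and the statement about improvement in some or all outcomes, on the pattern of estimates and intervals across all outcomes rather than on any one rejection or favourable result.

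The cost is wording and the reporting of estimates that the planned models already produce. No further participants, visits or data are needed. The downside is that fewer nominal rejections can be cited.

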Aim 3	Explore the independent effects of weight loss or diet quality on changes in plasma biomarkers related to AD, cerebral antioxidants and brain volume, and cognitive function across 12 months.

Abbreviation: AD, Alzheimer's disease.

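### Aim 3 reads rejection of weight loss against weight loss plus diet as showing that both are needed, but that test never examines weight loss, so a biomarker driven by diet alone would be reported as needing both

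*Protocol article*

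**What the plan says.** Aim 3 in Table 1 (Protocol article, Overview of study design, 2.1) is to "Explore the independent effects of weight loss or diet quality on changes in plasma biomarkers related to AD", and on brain measures and cognition. The Analysis section (2.9.2) assigns this to a set of nested likelihood ratio tests and gives their purpose: "The goal of this analysis is to determine if weight loss, diet quality or both should be targeted in future trials". That allows three answers.

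The section then says why no multiplicity adjustment is made for these tests, and in doing so states how a rejection is to be read: "rejection of any of the nested comparisons will imply that a change in a greater number of underlying covariates", the example being that "weight loss and diet compared to weight loss alone are needed to elicit changes in biomarkers". It does not list the models to be compared or say how several results are to be read together.

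The Discussion adds that, if the pilot suggests an independent effect of diet quality, the team will also propose a trial to "investigate the impact of improved diet quality without weight loss on AD outcomes".

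**The concern.** The null hypothesis of weight loss against weight loss plus diet is that the diet coefficient is zero given weight loss. Rejecting it is evidence about diet. It is no evidence about weight loss, whose coefficient is free in both models. If diet quality alone drives a biomarker, the comparison is right to reject, but the conclusion the plan attaches to it, that both are needed, is false.

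The pattern that most clearly supports a diet-only trial is that diet adds to weight loss and weight loss adds nothing to diet. Under the stated reading, the first half of that pattern is already taken as a case for both. Aim 3 exists to choose the target of the next trial, so the error falls on the decision the analysis is meant to inform.

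This is not a multiplicity problem. It arises for a single outcome, on a true positive, and no change of significance level removes it.

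**Working it through.** The plan gives no significance level, effect size, correlation or power for Aim 3, so there is no figure of its own to reproduce. The logic needs no numbers; the calculation below shows how often it would matter.

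**Inputs from the Protocol article (Sample size, 2.9.1).** The section plans "with a sample size of 81" and 20% attrition: 81 × 0.8 = 64.8, taken as n = 65.

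**Assumed, not in the document.** Each test at the 5% level; one 12-month change score per participant; weight change W and diet-quality change D standardised, with correlation ρ of 0.3 to 0.7; outcome y with variance 1; diet-only slope b of 0.3 or 0.5 SD per SD; no other covariates.

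**Model and test.** y = b₀ + b_W·W + b_D·D + error. For W against W + D the statistic is n·ln(RSS_W / RSS_WD), compared with 3.84 (chi-square, 1 df).

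**Chance that the plan's own comparison rejects when b_W = 0.** The noncentrality is λ = n·b²·(1 − ρ²)/(1 − b²), and the rejection probability is approximately Φ(√λ − 1.96).

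| b | ρ | λ | Approximation | Simulation |
|---|---|---|---|---|
| 0.3 | 0.3 | 65 × 0.09 × 0.91 / 0.91 = 5.85 | Φ(0.46) = 68% | about 66% |
| 0.3 | 0.5 | 65 × 0.09 × 0.75 / 0.91 = 4.82 | Φ(0.24) = 59% | about 59% |
| 0.3 | 0.7 | 65 × 0.09 × 0.51 / 0.91 = 3.28 | Φ(−0.15) = 44% | about 44% |
| 0.5 | 0.5 | 65 × 0.25 × 0.75 / 0.75 = 16.25 | Φ(2.07) = 98% | about 97% |

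Repeat simulations differ by about one percentage point. Each of these rejections is a correct finding about diet that the plan would word as a need for both.

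**What the reverse test would show.** In the same diet-only scenarios, D against W + D rejects in about 5% to 6% of trials, close to its nominal level. The data therefore usually give no sign of a weight-loss contribution, but the stated reading does not use that.

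**Requiring both partial tests to reject.** At ρ = 0.5 a diet-only biomarker is then called both in about 3% of trials (b = 0.3) or 5% (b = 0.5).

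**The price.** If both slopes are truly 0.3 and ρ = 0.5, the residual variance is 1 − (0.09 + 0.09 + 2 × 0.5 × 0.09) = 0.73. Each partial test then has λ = 65 × 0.09 × 0.75 / 0.73 = 6.01 and rejects in about Φ(0.49) = 69% of trials (67% by simulation). Both reject together in about 40%. Exactly one rejects in about 2 × (67% − 40%) = 54%, so a single rejection must not be read as showing that the other factor has no effect.

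**The weight-only case.** If weight loss alone acts, the plan's stated comparison rejects in only about 5% to 6% of trials. The error appears only if D against W + D is also in the set. Reading any rejection as both would then be wrong in about 61% of trials at 0.3 SD and ρ = 0.5.

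**The case against.** The strongest reply is that the sentence justifies omitting a multiplicity adjustment and is not offered as a rule for choosing a target. The preceding sentence keeps three answers open, nothing forbids reading the comparisons together, and a condensed article may leave the model list to a fuller document. The Discussion would respond to an independent diet effect by proposing a diet-only trial, which suggests that the authors may read that pattern correctly in practice.

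Much of this stands. The absence of a model list is not a fault here. A rejection of no factor against one factor is not affected, so a reader might infer that the rule can never separate one factor from both; the document does not support that. A reader might also infer that a weight-only biomarker is misread in the same way. That needs a comparison which the wording suggests but does not state. The text says that rejection implies a need, which is weaker than proof, and the aim is exploratory.

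What does not stand is the defence of the example itself. The article states how a rejection of weight loss against weight loss plus diet will be read, and that reading does not follow from the test. Nor is it harmless as a reason for making no adjustment: it is the only reason given for Aim 3, and it rests on the same mistaken inference. The sensible response in the Discussion makes the inconsistency plainer, because the two sections draw different conclusions from the same result.

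**Conclusion.** The concern holds for the comparison that the plan itself gives. Rejecting weight loss against weight loss plus diet supports a contribution of diet quality and leaves weight loss untested, so a diet-only biomarker would be reported as needing both. Under the assumed inputs this happens in about 44% to 66% of trials at a 0.3 SD effect with correlation 0.3 to 0.7, and in about 97% at 0.5 SD with correlation 0.5. The percentages depend on those assumptions and on a single-change-score simplification of the analysis; the imaging outcomes, measured in a subsample, would have fewer participants. The logical error depends on none of this.

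The primary aim and the between-arm estimates are not affected. The wording should be corrected because Aim 3 is meant to steer the choice of the next trial.

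**What to change.** Replace the sentence on rejection of any nested comparison with:

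> For each outcome, fit the joint model and test (a) neither factor versus both (2 df), (b) diet given weight, and (c) weight given diet. Conclude that both contribute only if (b) and (c) both reject. If only one rejects, conclude evidence for that factor, without concluding that the other has no effect. If neither (b) nor (c) rejects but (a) does, the factors cannot be separated. If none rejects, there is no evidence for either. Report both partial coefficients with 95% CIs.

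Test (a) is needed so that two factors which cannot be told apart are not confused with two factors that show no effect.

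Drop the present reason for making no multiplicity adjustment in Aim 3; the exploratory status of the aim can be given instead.

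This is a change of wording. It needs no new data and at most one further model, the one with neither factor. The cost is the lower rate of concluding both shown above, which is why the partial coefficients and their intervals should carry the message rather than the test results alone.
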